### Data synthesis and analysis

We will summarize demographic characteristics of the samples and will perform a descriptive analysis of endpoints and other relevant clinical variables. Quantitative variables will be summarized using means, standard deviation, median and interquartile range. Categorical variables will be analysed using frequencies and proportions. We will analyze the mechanisms that contribute to missing data, which will guide subsequent imputation methods to address missingness. An accuracy analysis will be performed for both study groups (children and PLHIV) with bacteriologically confirmed tuberculosis as a reference standard and qPCR assay on stool as the index test under evaluation. We will calculate sensitivity *(primary endpoint)* and other test parameters: specificity, PPV and NPV, of the qPCR test compared to composite reference standard that includes any of the other tests positive (including induced sputum and gastric aspirate Xpert Ultra and MGIT culture, stool Ultra or LF-LAM). We will also calculate sensitivity (and other parameters: specificity, PPV and NPV) of the qPCR test *(secondary endpoint)* with respect to a clinical case definition. Accuracy will also be assessed for stool qPCR and each of the other microbiological confirmation tests separately against the clinical case definition (*secondary endpoint)*, in order to compare the performance of each test.

### Power and sample size

Sample size calculations were based on the primary endpoint to compare the qPCR assay performance to the bacteriological composite reference standard. Calculations were performed based on the following assumptions: (1) A proportion of laboratory confirmed TB of 8.5% in the pediatric cohort and 20% in the adult cohort. (2) 80% sensitivity of qPCR against the composite reference standard with a precision of 7.5% around the estimate in the child cohort and 7% in the adult cohort. According to these assumptions, the required sample size for the cohort is 1295 children (525 in Mozambique and Uganda and 245 in Eswatini), and 650 adults (250 in Eswatini and Mozambique and 150 in Uganda).

### Biorepository

Baseline samples, including remaining respiratory, stool, urine, and blood samples, will be frozen and stored at the study site laboratory. The trial provides a unique opportunity to investigate a number of TB biomarkers, which could discriminate active disease from TB infection as well as TB from non-TB pneumonia using transcriptomic approaches. It also allows future studies on *M.tb* molecular epidemiology, and further characterization of the proteomic, metabolic and immunologic profiles of children presenting with signs of severe pneumonia, with or without TB. Biological samples will be retained for 10 years after study completion, unless there are objections expressed by the adult participant and children’s parent(s)/guardian(s).

## Discussion

This study is designed to evaluate a new diagnostic test that aims to improve molecular confirmation of TB as well as provide a new monitoring tool for treatment response in children and PLHIV. To date, studies using stool as a target sample have been done with already existing molecular tests like Xpert and Xpert Ultra using stool, but few of those studies propose novel molecular platforms for validation or exclusively include the vulnerable populations of intended use (children or PLHIV with presumptive TB). Therefore, the relevance of this study relies not only on the use of stool as a sample for bacteriological confirmation, but also on the molecular non-Xpert based approach to it, as there is need for improvement molecular stool diagnostics. Further, the design is aligned with the latest WHO guidelines on diagnosis and management of TB in children and adolescents that, for the first time, include stool as a valid sample for TB testing. In fact, apart from the classical approach of using culture in a respiratory sample as a reference standard, we will assess the performance of this new diagnostic test against a robust composite reference standard that includes culture and Xpert Ultra in respiratory samples, Xpert Ultra in stool and LF-LAM in urine and against clinical diagnosis. In this way, we will both maximize the bacteriological confirmation and estimate the potential increase in bacteriological confirmation in those cases that start treatment in the absence of bacteriologic confirmation. It will also allow to see the contribution of each single TB test to bacteriological confirmation, including the expected additionality of que novel stool-based qPCR (all other test negative but qPCR positive).

Another relevant strength in the study design is the two week and two-month longitudinal follow-up to verify baseline disease classification in participants who do not initiate treatment. This will play a relevant role in both increasing the number of confirmed cases (after resampling if persistence of symptoms), but also in the reliability of the specificity estimations (only those who have tested negative at baseline, who did not start treatment and who do not present symptoms after 2 months will be classified as “unlikely TB”).

The study is designed to include those presumptive TB cases already detected by the routine procedures of the national TB programs or healthcare system workers and does not include those identified in community screening programs. Therefore, recruitment will rely on the performance of the already existing platforms for TB detection. While this is good practice and prevents the study from negatively impacting future clinical practice, the COVID-19 pandemic has impacted TB notifications in many study settings [1]. This may impact recruitment and the capacity to attain the expected sample size.

Though stool has already been recommended by the WHO as a sample for bacteriological confirmation in children, the implementation of stool-based diagnostics has not yet been widespread. Therefore, this study is highly relevant as it uses stool as the preferred sample. Also, the new qPCR platform has the potential to lower the limit of detection of Mtb in stool compared to currently available tests. If our project successfully demonstrates an increase in bacteriological confirmation, this platform has the potential to be adapted to a field-friendly point-of-care test that could be easily implemented in basic health care centers in Sub-Saharan Africa or resource-limited countries, in line with the priorities of the End TB strategy [38]. As a multi-national study with different epidemiological and environmental backgrounds, one can expect to face variability, but this will make results more robust and able to be applied in different environments.

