### Study design

This is a multi-national, prospective, diagnostic evaluation study with a nested longitudinal cohort evaluation. The total duration of the study will be 60 months, with a 30-month recruitment period in which different samples will be collected at baseline to assess the diagnostic performance of the qPCR assay. Recruitment in adults began November 2021 and will end by May 2024. In children recruitment began in April 2022 and will end by September 2024. All participants initiating TB treatment will be followed until treatment completion in order to assess treatment outcomes and the potential of the qPCR assay to be used as a treatment monitoring tool. Those participants not initiating TB treatment will be followed for 2 months after recruitment to accurately rule out TB diagnosis.

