### Study population

Participants ≥ 15 years of age living with HIV and children less than 8 years of age (irrespective of HIV status) presenting with signs and symptoms of presumptive TB to the entry points of the selected sites will be referred to the study team. Individuals with presumptive TB or their guardians if they are under 18 years old will be invited to complete informed consent and participate in the study after screening has ensured that they meet the study inclusion criteria. Participants from 15 to 17 years old will be also required to assent in order to enter the study.

Participants will be eligible for the adult cohort based on the following inclusion criteria: a) 15 or more years of age, b) confirmed HIV infection (antibody-based or molecular test), and c) reporting any of the following symptoms: cough, fever, night sweats or unintentional weight loss (any duration).

Children will be included in the study if: a) age under 8 years of age irrespective of HIV status, and b) reporting any of the following symptoms: 1) Persistent unremitting cough (or cough significantly worse than usual in child with chronic lung disease including HIV-related) of > 2 weeks duration, unresponsive to a course of appropriate antibiotics (when clinically indicated); 2) Poor growth documented over the preceding 3 months [clear deviation from a previous growth trajectory and/or documented crossing of centile lines in the preceding 3 months and/or; weight-for-age, or weight-for-height Z-score of ≤ 2 in the absence of information on previous/recent growth trajectory AND not responding to nutritional rehabilitation (or to antiretroviral therapy if HIV-infected)]. 3) Persistent unexplained lethargy or reduced playfulness/activity reported by the caregiver. 4) Persistent (> 1w) unexplained fever (> 38C), reported by a guardian or objectively recorded at least once. 5) In infants 0–60 days, also: unresponsive neonatal pneumonia or unexplained hepatosplenomegaly OR sepsis-like illness (all other more common causes excluded and/or not responding to appropriate therapy/ broad-spectrum antibiotics/antivirals) [33] (see Fig. 1).

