### Endpoints

#### Definitions

For analysis, the participants in the pediatric cohort will be classified as ‘confirmed tuberculosis’, ‘unconfirmed tuberculosis’ and ‘unlikely tuberculosis’ according international consensus pediatric endpoint definitions [22].  “TB case” definition will include both ‘confirmed’ and ‘unconfirmed’ tuberculosis. “Unlikely TB” will be used as reference for specificity (see Table 2).

**Table 2 Tab2:** Definitions for the pediatric cohort

**TB case**	**“Confirmed tuberculosis”**	*M. tb* to be laboratory-confirmed (culture or NAAT-based assay) from at least 1 specimen or positive urine LAM
	**“Unconfirmed tuberculosis”**	Bacteriological confirmation not obtained and at least 2 of the following: 1. symptoms/signs suggestive of tuberculosis, 2. chest radiograph consistent with tuberculosis, 3. close tuberculosis exposure or immunologic evidence of *M. tuberculosis* infection 4. positive response to tuberculosis treatment (requires documented positive clinical response on tuberculosis treatment—no time duration specified)
**Not TB case**	**“Unlikely tuberculosis”**	bacteriological confirmation not obtained and criteria for “unconfirmed tuberculosis” not met

For the adult cohort participants will be classified as “bacteriologically confirmed TB” or “clinically diagnosed TB”. “TB case” definition will be equivalent to decision to start treatment irrespective of bacteriological confirmation so it will include both “bacteriologically confirmed TB” and “clinically diagnosed TB”

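### Table 2 and the Discussion give incompatible rules for paediatric 'unlikely TB', the specificity reference, and Table 2 has no step by which recovery without treatment rules TB out

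*Protocol article*

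**What the plan says.** Three parts of the protocol article bear on how a child is classified.

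- **Endpoints, Definitions, Table 2.** 'Unconfirmed tuberculosis' is "Bacteriological confirmation not obtained and at least 2 of the following", the four items being symptoms or signs, chest radiograph, "close tuberculosis exposure or immunologic evidence of" infection, and response to TB treatment. 'Unlikely tuberculosis' is "bacteriological confirmation not obtained and criteria for “unconfirmed tuberculosis” not met". The text above the table makes confirmed plus unconfirmed the 'TB case' and makes 'unlikely TB' the reference for specificity. Neither class depends on whether treatment was started or on symptoms at 2 months.
- **Discussion.** 'Unlikely TB' is restricted to "only those who have tested negative at baseline, who did not start treatment and who do not present symptoms after 2 months".
- **Study design.** Participants who do not start treatment are to be "followed for 2 months after recruitment to accurately rule out TB diagnosis". The section on study visits and the Discussion give the same purpose in other words: establishing that the participant is TB-free, and verifying the baseline classification.

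Under Study population, children are referred when "presenting with signs and symptoms of presumptive TB to the entry points" of the sites, and each must report at least one listed symptom to be included.

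**The concern.** Table 2 is exhaustive: a child who is neither confirmed nor unconfirmed is 'unlikely'. The Discussion adds two conditions, no treatment and no symptoms at 2 months, and says nothing about children who fail them. The two rules therefore give different specificity denominators. They differ over the children whose TB-free status is least certain, so including or excluding them can move the specificity estimate.

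A second problem lies within Table 2. Because entry requires symptoms, nearly every child meets the symptom item at baseline, and one further baseline item makes a 'TB case'. Nothing in the table lets recovery without treatment reverse that. Its only item drawn from follow-up is response to TB treatment, which cannot apply to an untreated child. 'TB case' is the reference for the secondary comparison of qPCR with every other test, so the choice of rule could change those results. If it is settled only after qPCR results are known, the reported accuracy depends on a choice made late.

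**Working it through.** **Step 1: compare the two rules child by child.** Take a child with negative bacteriology, including any 2-month resampling, and symptoms at entry. Vary the radiograph (yes/no), exposure or immunologic evidence (yes/no), treatment (yes/no), documented response if treated (yes/no), and symptoms at 2 months (yes/no). That gives 2 × 2 × 3 × 2 = 24 profiles, where 3 counts untreated, treated with response, and treated without response. For the comparison, the Discussion's conditions are first read as sufficient. The rules disagree on 6 profiles:

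| Profiles | Table 2 | Discussion |
|---|---|---|
| Symptoms only, untreated, still symptomatic at 2 months (1) | unlikely | not unlikely, no class |
| Symptoms only, treated, no documented response, with or without symptoms at 2 months (2) | unlikely | not unlikely, no class |
| Untreated, well at 2 months, with radiograph, exposure/immunologic evidence, or both (3) | unconfirmed, so TB case | meets all three conditions |

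The first three conflict on any reading of the Discussion. The last three conflict only if its conditions are sufficient and not merely necessary. A symptoms-only child lost before 2 months is a further case outside the 24: Table 2 gives 'unlikely', while the Discussion's condition cannot be shown to be met.

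**Step 2: size of the second problem.** The plan states no figure to reproduce here, so this is an illustration.

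From the protocol (Power and sample size): 1295 children, 8.5% confirmed, 80% sensitivity. Confirmed = 1295 × 0.085 ≈ 110; qPCR-positive among them = 0.80 × 110 = 88; not confirmed = 1295 − 110 = 1185.

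Assumed:
- *e*, the share of the 1185 with exposure or immunologic evidence: 20% or 40%.
- *w*, the share of those who are untreated and well at 2 months: 10% or 50%.
- qPCR positivity of 1% in the well and 19% in the other unconfirmed children. The 19% borrows the gain in confirmation among children in the pilot study (Background) as a proxy.

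With U = 1185 × e and W = w × U:

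- Table 2 as written: sensitivity = [88 + 0.19(U − W) + 0.01W] / (110 + U)
- Recovered children counted as non-cases: sensitivity = [88 + 0.19(U − W)] / (110 + U − W)

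| e | w | U | W | Table 2 | Recovered as non-cases | Difference |
|---|---|---|---|---|---|---|
| 20% | 10% | 237 | 23.7 | 128.8/347 = 37.1% | 128.5/323.3 = 39.8% | 2.6 points |
| 40% | 10% | 474 | 47.4 | 169.5/584 = 29.0% | 169.1/536.6 = 31.5% | 2.5 points |
| 20% | 50% | 237 | 118.5 | 111.7/347 = 32.2% | 110.5/228.5 = 48.4% | 16.2 points |
| 40% | 50% | 474 | 237 | 135.4/584 = 23.2% | 133.0/347 = 38.3% | 15.2 points |

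Differences are taken before rounding. The result is driven by *w*, for which the documents give no value; *e* matters little.

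**Step 3: the first problem.** The documents give no count of symptoms-only children who stay symptomatic, are treated without response, or are lost, so the shift in specificity cannot be sized.

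**The case against.** The strongest reply is that the Discussion's wording states necessary conditions. Read as additions to Table 2, they only narrow the specificity group and do not turn a recovered child with exposure or a suggestive radiograph into 'unlikely TB'. That stands: a reader might infer that the Discussion plainly calls such a child 'unlikely', but the text does not settle it. The reply does not remove the symptoms-only conflict, because Table 2 still classes those children as 'unlikely' and the Discussion still excludes them.

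It can also be said that Table 2 follows cited international consensus definitions, so counting recovered children as cases is a considered choice. That is a fair reason to keep the consensus classes. It does not explain why follow-up is said to rule TB out when the table has no step that does so.

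Nor is follow-up unused. Untreated children still symptomatic at 2 months are fully resampled, and a positive result makes them confirmed. What is missing is narrower: use of follow-up to rule TB out.

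Finally, loss before 2 months is partly a missing-data matter, and the analysis section promises to study missingness and impute accordingly. That answers how a missing 2-month status might be filled in, but not which of the two rules then applies.

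**Conclusion.** The point holds as an inconsistency between two stated definitions. On any reading, the specificity reference differs between Table 2 and the Discussion for symptoms-only children who remain symptomatic, were treated without documented response, or were lost before 2 months. Separately, Table 2 counts an untreated, recovered child with entry symptoms and one more baseline item as a TB case.

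The reach is limited. Primary sensitivity and the sample size rest on the bacteriological composite and are unaffected. So are adults, for whom 'TB case' means the decision to treat. The effect is on paediatric specificity with 'unlikely TB' as reference and on the secondary 'TB case' accuracy endpoints.

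Two stronger conclusions are not supported. One is that untreated children who recover count as cases in general: with symptoms alone, they are 'unlikely' under both texts. The other is that the definition by itself produces a swing of 15 to 16 points: that needs half of the unconfirmed children to be untreated and well. At 10% it is about 2.5 points, and the documents do not say where in that range the study lies.

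**What to change.** Before analysis, reconcile Table 2 and the Discussion into one mutually exclusive, exhaustive analysis classification.

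1. Keep the Table 2 classes as the consensus classification.
2. Define the specificity reference as Table 2 'unlikely', no TB treatment started, and symptom-free at 2 months.
3. Put 'unlikely' children who fail those conditions, or whose status on them is unknown, in a separate 'unclassifiable' group. Leave it out of the specificity denominator and bound its effect by counting the whole group once as cases and once as non-cases.
4. Report a sensitivity analysis in which untreated children who are well at 2 months, and who meet 'unconfirmed' only through entry symptoms plus one other baseline item, are counted as non-cases. Those with both a suggestive radiograph and exposure or immunologic evidence remain cases.

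The change is to analysis wording only. Treatment start and 2-month status are already collected under the schedule of events, and no participant's care changes. The cost is a somewhat smaller specificity denominator, hence a slightly wider interval. Results under the unmodified Table 2 can be shown alongside for comparison with other studies.

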## Data Availability

This is not applicable as it is a study protocol.
